## Abstract

Emotional distress (depression, anxiety, and PTS) and unhealthy lifestyle factors (e.g., smoking, alcohol consumption, poor diet, limited physical activity, medication adherence) are common in hemorrhagic stroke (HS) survivors and may increase risk for recurrence, morbidity, and mortality. Emotional distress and unhealthy lifestyle factors tend to be interdependent between survivors and their informal caregivers (e.g., family and friends who provide unpaid care; together called dyads), such that one partner’s lifestyle and coping behaviors influence the other’s behaviors, yet no research has closely examined this relationship in HS dyads over time. We will conduct a mixed methods study to quantitatively and qualitatively understand the longitudinal relationship between emotional distress and lifestyle factors across time in this population (HS dyads) to identify treatment targets to prevent emotional distress chronicity and stroke recurrence. In aim 1, we will assess emotional distress (i.e., depression, anxiety, and PTS) and lifestyle factors (smoking, alcohol consumption, poor diet, limited physical activity medication adherence/blood pressure control) in dyads of survivors of HS and their caregivers (N = 80), at three separate time points (hospitalization in the Neuro-ICU, 1, and 3 months later). We hypothesize that 1) lifestyle factors and emotional distress will be interrelated within and across time for both survivors and caregivers, and 2) lifestyle factors and emotional distress will be interdependent between survivors and caregivers. We also aim to explore the nuanced interplay between lifestyle factors and emotional distress and gain in depth information on barriers and facilitators for a dyadic intervention to optimize lifestyle behaviors and emotional functioning in HS dyads. Eligible patients will be adults who have a caregiver also willing to participate. Patients will be referred for study participation by the nursing team who will ensure that they are cognitively able to meaningfully participate. Multilevel dyadic modeling (i.e., actor-partner interdependence model; APIM) with distinguishable dyads will be used to determine influences of these factors onto each other over time. In Aim 2, we will conduct live video qualitative dyadic interviews (N = 20 or until theme saturation) at all time points from the same participants with and without emotional distress and at least one lifestyle risk factor, to understand the nuanced relationships between emotional distress and lifestyle behaviors, and barriers and facilitators to engagement in a skills-based psychosocial intervention. Interviews will be analyzed using inductive and deductive approaches. The present study is currently ongoing. So far, we enrolled 2 participants. Recruitment will end October 2022 with plans to analyze data by December 2022. The findings from this study will be used to further develop psychosocial interventions and inform novel treatments for survivors of HS and their informal caregivers.

## Introduction

Hemorrhagic strokes (HS) account for less than a quarter of all strokes yet are some of the deadliest and most debilitating forms of cerebrovascular disease [1]. Despite static risk factors (e.g., age, ethnicity, education, medical/mental health history) and post-stroke medical events (e.g., delayed infarction, pneumonia, sepsis) contributing to poor overall quality of life in approximately 1/3 of survivors with HS [2], there are clear modifiable risk factors, including lifestyle (e.g., smoking, alcohol consumption, poor diet, limited physical activity, medication adherence/blood pressure control) [3–8] and emotional distress (depression [9], anxiety [10–12], and post-traumatic stress [13, 14]) which may improve health outcomes post-HS [8]. Unfortunately, HS survivors receive very little emotional-behavioral support after illness onset [2], and research is limited on the interplay between lifestyle factors and emotional distress post-stroke in this population.

Along with survivors [15–18], informal caregivers can also develop chronic psychosocial sequelae in the form of depression, anxiety and PTS [17, 19–22]. Our prior research with patients with acute brain injury hospitalized in the Neuro-ICU suggests dyadic interdependence, such that one partner’s coping and emotional function influence the other’s over time [23–25]. Research in other populations suggests a very similar dyadic interdependence for lifestyle factors [26, 27]. Although our previous studies demonstrate the benefits of a dyadic approach in an acute neurological illness population for emotional distress [23–25, 28–30], there have been no studies incorporating lifestyle and emotional distress factors simultaneously in one treatment modality, nor prospective data which specifically links these two modifiable domains to a conceptual model for treatment targets in HS dyads. Moreover, current psychosocial interventions with neurological disorders are typically focused either on survivor or caregiver outcomes and are not sensitive to the specific needs of HS dyads, which usually include greater physical and psychosocial sequelae, symptom burden, higher recurrence risk, and substantial disability, morbidity, and mortality.

Based on the limited research, a dyadic approach to improving outcomes in HS survivors and caregivers is ideal because: 1) the HS event can serve as a pivotal event whereby survivors and informal caregivers are highly motivated for immediate behavioral change; 2) informal caregivers are already involved in stroke care and can engage with interventions alongside the survivors. However, the interplay between these major modifiable factors over time, as well as the shared survivor-caregiver experiences from hospitalization through 3 months post stroke are not known.

Therefore, we aim to understand the longitudinal association between lifestyle factors and emotional distress among survivor-caregiver dyads from hospitalization in the Neuro-ICU (baseline) to 1 and 3 months later. We hypothesize that lifestyle factors and emotional distress will be interrelated within and across time for both survivors and caregivers and that these variables will be interdependent between survivors and caregivers within and across time [31]. We also aim to understand the nuanced interplay between lifestyle factors and emotional distress and gain in depth qualitative information on barriers and facilitators for a dyadic intervention to optimize lifestyle behaviors and emotional functioning in HS dyads.

## Methods

### Study design

This is a mixed methods study designed to examine the longitudinal association between lifestyle factors and emotional distress among hemorrhagic stroke survivor-caregiver dyads from hospitalization (baseline), 1 and 3 months later. The quantitative and qualitative information gathered from this research will be used to develop a dyadic psychosocial intervention to optimize recovery for patients with HS and their caregivers. All ethical guidelines have been met and ethical approval from the Massachusetts General Hospital (MGH) institutions IRB has been secured (approved 07/29/2021; Protocol # 2021P001923). Per our IRB’s informed consent policy, our research study only includes interactions involving survey procedures and thereby does not require written or oral consent if consent is implied as part of beginning the survey document. An informational fact sheet will be administered to each participant to explain the purposes of the study and outlines the level of participation requested.

### Setting

Recruitment and procedure implementation will occur at the Neuro-ICU at MGH, a northeastern academic medical facility. The Neuro-ICU at MGH sees approximately 170 survivors with HS annually (~100 ICH, ~70 SAH; based on personal correspondence with Neuro-ICU Medical Director). The MGH Neuro-ICU contains 22 patient rooms and is staffed by ~80 Neurointensive Care Nurses and a Clinical Nurse Specialist. Physician coverage is provided by two teams of fellows, residents, and board-certified Neurointensive Care attendings. Coverage is provided 24 hours per day/7 days per week by fellows and residents. Approximately 1700 patients with an acute neurological condition are seen yearly in the MGH Neuro-ICU, with approximately 170 of these admissions related to hemorrhagic stroke, ensuring participant enrollment is feasible and consistent with the study timeline.

### Inclusion/Exclusion criteria

Each member of the survivor-caregiver dyad must meet the eligibility criteria to enroll in the study. The survivor must be diagnosed with HS and admitted to the Neuro-ICU, 18 years of age or older, English speaking, have a life expectancy above 3 months, and cognitively intact as judged by the nursing team. The caregiver must be responsible for the informal aftercare of a survivor admitted, 18 years of age or older, and English speaking. Inclusion and exclusion criteria can be view in Table 1.

**Table 1 pone.0261635.t001:** Hemorrhagic stroke survivor and caregiver inclusion criteria for present study.

Survivor Eligibility Criteria	Caregiver Eligibility Criteria
• Diagnosis of Hemorrhagic Stroke.	• Informal caregiver to survivor admitted to Neuro-ICU for Hemorrhagic Stroke
• Admitted to Neuro-ICU.	• 18+ years of age.
• 18+ years of age.	• English speaking.
• English speaking.	
• Life expectancy above 3 months.	
• Cognitively intact as judged by the nursing team.	

### Recruitment

Recruitment will occur at bedside in the Neuro-ICU at Massachusetts General Hospital (MGH). We will recruit participants through referrals from the nursing team of the Neuro-ICU at MGH from morning unit rounds. Survivors who express interest in the study and their respective caregivers will meet either in person or virtually (phone or video call for COVID-19 safety efforts if required) with a study research assistant to learn more about the study and be screened for eligibility. Those who wish to participate will be given information about the study as part of an informed consent process, as well as a resource sheet with the Principal Investigator’s (PI) contact information. These procedures (see Fig 1) will be completed in the survivor’s private hospital room. All dyads will be recruited within the first week of the survivor’s admission in the Neuro-ICU. We will recruit 80 dyads (80 survivors and 80 caregivers) over the course of 12 months. We have used this strategy successfully with previous studies within the Neuro-ICU and have had success with virtual data collection [28, 30, 32].

**Fig 1 pone.0261635.g001:**
[figure not shown]
Study flow and design. CRC = Clinical research coordinator; ICU = Intensive Care Unit, ARN = Attending registered nurse, BSN = Bedside registered nurse. Above shows the flow of study recruitment. Recruitment will begin at bedside in the Neuro-ICU at MGH. We will recruit participants through referrals from the nursing team of the Neuro-ICU at MGH from morning unit rounds. Survivors who express interest in the study and their respective caregivers will meet either in person or virtually with a study research assistant to learn more about the study and be screened for eligibility. Those who wish to participate will be given information about the study as part of an informed consent process. The research assistant will administer surveys at bedside via iPad. The CRC will follow up for future surveys at 1 and 3 months. Interested caregivers will be given the opportunity to participate in qualitative interviews at 3 months.

### Screening and enrollment

The clinical research coordinator (CRC) will obtain consent via an IRB-approved facts sheet (i.e., implied consent) delivered at time of study introduction. Participants are considered enrolled in the study when they have read over the fact sheet and begin the electronic survey if they chose to do so. The CRC will schedule a time with enrolled participants for their survey completion and potential interview in future follow-ups (one- or three-month timepoints for coordination of interview times). We will provide an additional overview of study procedures at the beginning of the interview. The study interviewer will ensure that participants understand the study procedures and that the interviewer will audio-record the interview.

### Considerations for participant safety during study participation

If a participant reports thoughts of self-harm or suicidality at any point during the study, the CRC will notify the PI. The PI will contact the participant within 24 hours to conduct a risk assessment. The PI will initiate psychiatric consults as needed. Participants who are determined to need intervention will be provided with information about resources for care. Participants who do not require higher levels of care may continue in the study. Safety will always be prioritized over study participation.

#### Assessments

For Aim 1, participants will complete online surveys through REDCap [33]. All measurements are presented below in Table 2. For the initial survey, participants may elect to either complete the surveys at bedside using an iPad or be e-mailed a secure REDCap link to complete the surveys at a later scheduled time [33]. The CRC will be available during the assessment to answer questions and provide assistance as needed/requested. For the latter two surveys, the CRC will e-mail the survey to participants via a secure REDCap links [33]. The CRC will offer to help over the phone during the latter two time points if needed/requested. If a consented participant does not complete the surveys after one week, the CRC will contact the participant via phone call and assist with completing the questionnaires over the phone. Any participants who are unreachable by the second full week (i.e., 14 days) after being e-mailed their survey link will be deemed lost to follow-up.

**Table 2 pone.0261635.t002:** Study measures.

Construct	Measure	Participant
Demographic	Age, gender, race, education yearly income, and marital status	Both
Functional Impact	Modified Rankin Scale [34]	Survivor only
Functional Impact	Barthel Index [34]	Survivor only
Emotional Distress	Hospital Anxiety and Depression Scale [35]	Both
Emotional Distress	Post-Traumatic Stress Checklist– 5 [36]	Both
Emotional Distress	Perceived Stress Scale [37]	Both
Emotional Distress	UCLA Loneliness Scale [38]	Both
Functional Impact	PROMIS Physical Function [39]	Both
Functional Impact	PROMIS Emotional Support [39]	Both
Functional Impact	PROMIS Social Isolation [39]	Both
Resiliency	Cognitive and Affective Mindfulness Scale [40]	Both
Resiliency	Measure of Current Status [41]	Both
Resiliency	Intimate Bond Measure [42]	Both
Resiliency	Caregiver Self-Efficacy [43]	Caregiver only
Resiliency	Preparedness for Caregiver [44]	Caregiver only
Lifestyle	Godin Leisure-Time Exercise Questionnaire [45]	Both
Lifestyle	Mediterranean Eating Questionnaire [46]	Both
Lifestyle	Pittsburgh Sleep Quality Index [47]	Both
Lifestyle	Jenkins Sleep Questionnaire [48]	Both
Lifestyle	Morisky Medication Adherence Scale [49]	Both
Lifestyle	The Fagerström Test for Nicotine Dependence [50]	Both
Lifestyle	Alcohol Use Dx Ident. Test-Consumption [9]	Both

For Aim 2, we will conduct participant interviews through secure video platform Zoom. We will audio-record, transcribe, and code the interviews. Participants will be recruited for interviews after they have completed the final survey at three months. We will attempt to recruit dyads where both participants reported at least one lifestyle risk factor and either high or low emotional distress. Given the elective nature of this interview, completion of the interview will be based on the convenience sample of those selecting to participate.

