### Procedures

We will recruit 80 dyads (80 survivors and 80 caregivers) over the course of 12 months. Potential participants will be referred by the nursing team from unit rounds. The PI will give presentations to the nursing team to engage them as partners of the research and to make appropriate referrals for the study. Survivors who express interest in the study and their respective caregivers will meet either in person or virtually (phone or video call for COVID-19 safety efforts) with a CRC to learn more about the study and be screened for eligibility. Those who wish to participate will be given more information about the study as part of the consent and enrollment process. As mentioned earlier, dyads will be recruited within the first week of the survivor’s admission in the Neuro-ICU.

After determining eligibility study staff will meet with potential dyads to review the fact sheet for passive consent. After the document has been reviewed, study staff will answer any questions the participants may have. Participants will receive a description of all study procedures, information about potential risks and benefits of participation, and study contact information (including that of the IRB) in case questions arise at a later time. The fact sheet will also explicitly state that study participation is voluntary, and that participants may refuse to answer any questions that make them uncomfortable and may discontinue participation at any time. As consent is a continuous process, participants will be given a copy of the fact sheet and will be invited to ask questions about their participation at any point over the course of the study. In addition, participants will be assured that withdrawal from the study will not compromise their medical care in any way. Consent and authorization will be implied by voluntary completion of the survey (approved by the MGH IRB).

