**Fig 2 pone.0261635.g002:**
[figure not shown]
APIM design and study measures. Above describes the actor-partner interdependence model (APIM) and assessments used in our study. Multilevel dyadic modeling (i.e. APIM) with distinguishable dyads will be used to determine influences of lifestyle and emotional distress factors onto each other over time and within the dyad. We will administer lifestyle and emotional distress measures at each timepoint. In the context of this study, the actor effect is the impact of a person’s lifestyle and emotional distress factors on his/her own lifestyle and emotional distress at 1 and 3 months. Similarly, the partner effect is the impact of a person’s factors on his/her partner’s same variables at 1 and 3 months.

In Aim 2, we will conduct live video qualitative dyadic interviews (N = 20 or until saturation) at the same time points from participants (ICH and SAH stratified) with and without emotional distress and at least one lifestyle risk factor to understand the nuanced relationships between emotional distress and lifestyle behaviors, and barriers and facilitators to engagement in a skills-based psychosocial intervention. All qualitative data will be analyzed in NVivo 10 [52] using a hybrid inductive-deductive analytic strategy [53]. Similar to other methods we have used, we will de-identify and transcribe interviews verbatim and upload to NVivo 10. We will construct the primary codebook consistent with study goals. Transcript coders will practice coding a single transcript and we will modify the initial codebook based on usability. On future transcripts, coders will meet to reconcile any disagreements and discuss coding strategy.

Coders will start with deductive a priori themes consistent with study aims (i.e., relationship between lifestyle and emotional distress after HS) and will flexibly add new codes inductively to enhance the codebook. We will construct queries using the NVivo matrix function (i.e., crosstabs) to interpret and contextualize the qualitative data. This hybrid analytic approach will allow us to extract findings within Survivor and caregiver themes and will help us gain better understanding of the relationship between lifestyle and emotional distress after HS in survivors and informal caregivers and inform future interventions targeting these variables simultaneously.

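### The medication adherence scale goes to every survivor and caregiver at each wave, but nobody is required to take medication and no listed measure records whether they do

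*Protocol article*

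**What the plan says.** The Abstract makes adherence one of the Aim 1 factors to be assessed in both partners: "lifestyle factors (smoking, alcohol consumption, poor diet, limited physical activity medication adherence/blood pressure control) in dyads of survivors of HS and their caregivers". Table 2, under Assessments, carries this through with the row "Morisky Medication Adherence Scale [49] Both". The same table restricts other instruments by role, for example "Preparedness for Caregiver [44] Caregiver only", so a restriction was available and was not applied to adherence. The text introducing Table 2 presents it as the list of all measurements, and no row asks whether the respondent takes prescribed medication.

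The caregiver criteria are short: "The caregiver must be responsible for the informal aftercare of a survivor admitted, 18 years of age or older, and English speaking". Nothing in them implies regular medication. The survivor criteria (Table 1) do not require medication before the stroke either.

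On timing, the Fig 2 caption says: "We will administer lifestyle and emotional distress measures at each timepoint". On the model, it says: "the partner effect is the impact of a person’s factors on his/her partner’s same variables at 1 and 3 months". Data analysis puts the dyads into a pairwise file, centres scores on the grand mean and converts them to z-scores. The planned size is given under Procedures: "We will recruit 80 dyads (80 survivors and 80 caregivers) over the course of 12 months".

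**The concern.** For smoking and alcohol, zero is a true value for a non-user. Adherence is different: a person with no doses to take has not adhered well or badly, and the construct does not apply. The stated design nevertheless calls for an adherence score from every survivor and caregiver at every wave.

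Two things could follow. If unmedicated people answer and are scored as having no lapses, the adherence variable mixes good adherence with absence of treatment. Absence of treatment may itself be related to the predictors, so the error need not be only noise. If they leave the scale blank, the file cannot separate people to whom it does not apply from people who did not respond.

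The same problem can arise over time in survivors. A survivor on no medication before the stroke may have no meaningful baseline adherence, yet Aim 1 explores trajectories from hospitalization. A first valid score at a later wave could then look like a change in behaviour.

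**Working it through.** The article gives no figure on this point to reproduce: no medication rate, and no alpha, power or effect size for the 80 dyads. What follows is illustration on stated assumptions.

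**Inputs from the article.** 80 dyads, 160 people (Procedures); adherence scale given to both (Table 2); partner effect on the same variables (Fig 2 caption); grand-mean centring and z-scores (Data analysis).

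**Assumed inputs.** Share q of caregivers on regular medication: 80%, 60% or 40%. Two-sided alpha 0.05 and power 0.80. No attrition.

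**1. Unmedicated caregivers set aside.** Dyads with a valid caregiver score: n = 80 × q. Smallest detectable correlation by Fisher z: r = tanh[(1.960 + 0.842)/√(n − 3)].

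| q | n | dyads without a caregiver score | detectable r |
|---|---|---|---|
| 100% | 80 | 0 | 0.31 |
| 80% | 64 | 16 | 0.34 |
| 60% | 48 | 32 | 0.40 |
| 40% | 32 | 48 | 0.48 |

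For example, at n = 48: 2.802/√45 = 0.418, and tanh(0.418) = 0.395.

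**2. Unmedicated caregivers scored as fully adherent, medication unrelated to the predictor.** Simulation of 1,000,000 pairs with a latent correlation of 0.30. Adherence is capped at a best score 1.0 or 1.5 SD above the mean, and unmedicated caregivers are placed at the cap.

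| q | observed r, cap 1.0 SD | observed r, cap 1.5 SD |
|---|---|---|
| 100% | 0.29 | 0.30 |
| 80% | 0.23 | 0.22 |
| 60% | 0.18 | 0.16 |
| 40% | 0.13 | 0.12 |

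The true association is diluted.

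**3. As in 2, but medication status related to the predictor.** With q = 60%, a latent slope of 0.5 from the predictor to being unmedicated, and no true link between predictor and adherence, the observed correlation is 0.22 (cap 1.0 SD) or 0.25 (cap 1.5 SD). An association appears where there is none, so the error can run in either direction.

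**4. Shift in the shared z-scale.** If scores are centred over all 160 people and every survivor has a valid score, the grand mean moves towards the best score by the unmedicated fraction of the gap between the two: 16/160 = 10%, 32/160 = 20% or 48/160 = 30% at q = 80%, 60% or 40%. The SD changes as well. This is a linear rescaling. In a model that uses only valid adherence scores it alters the intercept and the size of the standardised coefficient, but not the test of that coefficient.

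**Which effects are touched.** Effects that use an unmedicated member's adherence score, as predictor or outcome, are exposed to 1, 2 or 3. Survivor adherence predicted by distress or by either member's other behaviours, among medicated survivors, needs no caregiver adherence score and is exposed only to 4. Models for the other lifestyle measures that do not include adherence are not affected.

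**The case against.** The strongest reply is that Table 2 lists instruments, not items, skip logic or scoring. A branching question or a not-applicable code may exist in the survey build, the full protocol or an analysis plan, none of which is shown, and an article need not print it. A coordinator is also available to help respondents, and clinical information is drawn from the medical record.

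Much of this stands, and it rules out several stronger readings that a reader might infer:

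- *That an unmedicated caregiver will certainly be scored as a perfect adherer or lost.* The article gives no scoring rule, and how such a person answers depends on items and instructions that are not shown.
- *That the model would silently drop these dyads.* A pairwise file is a data layout, not a deletion rule. In a multilevel model a missing adherence outcome removes that outcome row, and further rows are lost only where the missing score serves as a predictor.
- *That the dyadic adherence effects cannot be interpreted.* Dyads with valid scores still inform them, with less precision.
- *That adherence must become a survivor-only outcome.* That would rewrite the dyadic hypothesis and is a preference, not something the defect requires.

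What does not stand is that the point is merely unprinted detail. The article does fix who completes the scale, when, and on which variables the partner effect is defined, and it names no subset for adherence. The medical record is that of the admitted survivor, so it is no evident source for a caregiver's medication. The right to refuse uncomfortable questions is not a not-applicable code, and would mix non-users with refusers. Medication status not asked at each wave may not be recoverable later.

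**Conclusion.** The point holds in limited form. As stated, the design calls for an adherence score from people for whom adherence may be undefined, and nothing shown identifies them. Effects that use those scores may be diluted or biased, or non-applicability may be confused with non-response; which of these occurs depends on a scoring rule the article does not give.

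The size is unknown, because the documents give no medication rate. Under assumed rates of 80%, 60% and 40%, a valid caregiver score exists in 64, 48 or 32 of 80 dyads before attrition. The simulated correlations further assume a latent value of 0.30, a capped score and, for the spurious association, a link between medication status and the predictor. They show that the effect can be material, not that it will be.

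Adherence is one of seven lifestyle instruments in Table 2, so Aim 1 as a whole is not undermined.

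**What to change.** - Before the scale at each wave, ask both members whether they are currently prescribed regular medication.
- Score the scale only if the answer is yes. Otherwise record not applicable, coded separately from missing and never as zero lapses.
- Standardise adherence among those with valid scores.
- Fit effects that use a member's adherence score only where that member is prescribed medication at the relevant wave, and report that number of dyads. This also keeps a survivor with no pre-stroke medication from contributing an artificial baseline score.

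The cost is one branching question in REDCap and a short addition to the analysis text. The downside is a smaller stated number of dyads for the model that uses adherence in both members. The article's Results report only four completed surveys (two survivors, two caregivers), so if the question is not already in the survey, adding it at that stage loses almost nothing.
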